**INTRODUCTION.**

Chest pain is one of the main reasons for cardiology consultation, reflecting the existence of ischemic heart disease. (1). However, in a high proportion of patients with myocardial ischemia, invasive tests do not document obstructive coronary lesions of the epicardial coronary arteries. (1,2).

In the coronary arterial circulation there is progressive branching of the vessels, constituting two distinct compartments that can be involved individually or in combination: a) the "macrovascular compartment" constituted by the epicardial arteries (conduction function); and b) the "microvascular compartment" constituted by the arterioles (flow regulatory function) and the capillaries (exchange function). Technological progress has made possible the development of new invasive physiological coronary indices that allow an exhaustive examination of both arterial compartments, making it possible to precisely discern their involvement. (2–5).

On the other hand, microRNAs (miRNAs) comprise a range of small fragments of noncoding RNA (nc-RNA) that influence post-transcriptional regulation of gene expression; their expression has been shown to be altered in ischemic heart disease (6). However, there are no research studies that comprehensively evaluate the role of miRNAs in relation to the affected coronary compartment (7).

Thus, our objective will be to prospectively evaluate the relationship of the different patterns of coronary involvement with the levels of circulating miRNAs.

**BACKGROUND**

**- Invasive physiological evaluation of the coronary circulation.**

[figure not shown]
 Coronary circulation is the set of vessels responsible for supplying oxygen- and nutrient-rich blood to the myocardium, and cardiac function being highly dependent on the maintenance and modulation of coronary flow. The myocardium is one of the tissues with the highest basal aerobic requirements in the body (8-10 mL O2/min/100 g in the myocardium vs. 0.15 mL O2/min/100 g in skeletal muscle) (3,8). At the anatomical level, coronary flow regulation is structured in two distinct compartments. On the one hand, there is the macrovascular compartment comprising arteries > 400 microns (conductance vessels) whose function is to distribute coronary flow to different territories, and on the other, the microvascular compartment comprising arteries < 400 microns, intermediate arterioles and small arterioles (resistance vessels) whose function is to regulate the amount of coronary flow, by vasodilation or vasoconstriction, that reaches the capillaries in which the exchange of nutrients and cellular waste takes place. (3,8).

*Illustration 1. Physiology of the coronary circulation.*

Hemodynamic studies on coronary blood circulation are based on "Poiseuille's Law" for hemodynamic circuits and its relation to "Ohm's Law" for electrical circuits. Based on these, it is established that the flow of fluid through a circuit is related proportionally to the pressure gradient across the circuit and inversely proportional to the resistance of the circuit (9).

| **Ohm´s Law** | | **Poiseuille´s Law** | |
| --- | --- | --- | --- |
| ΔVe  Ie =  Re | | ΔPcor ΔPcor  Qcor = =  RCor (8 μ L / π r^4^ ) | |
| Ie | Intensidad de Corriente | Qcor | Flujo Coronario |
| ΔVe | Gradiente de Voltaje Eléctrico | ΔPcor | Gradiente de Presión Transcoronario |
| Re | Resistencia Eléctrica | Rcor | Resistencia Coronaria |

Table 1. Equivalence between Ohm's Law and Poiseuille's Law

Under basal physiological conditions, the relationship between pressure and blood flow in the coronary arteries is not linear, with coronary flow remaining stable over a wide range of pressures. This phenomenon is known as "coronary autoregulation" (8). However, in situations of complete vasodilatation of resistance vessels, either physiologically induced by exercise or pharmacologically induced, for example, with adenosine, the relationship between pressure gradient and coronary flow becomes linear, allowing the application of the consequences of "Poiseuille's law” to obtain coronary physiological indices and thus assess coronary circulatory function (8,10).

**- Coronary Flow Reserve (CFR)**(11)

The increase in flow from the basal situation, where the "coronary autoregulation" mechanism governs, to the situation of maximum hyperemia, in which the coronary flow rate depends on the pressure gradient in the coronary circulation, is an excellent indicator of the functional state of the circulation, both at the macrovascular and microvascular levels. Under normal conditions, coronary circulation can increase more than five times in maximum hyperemia compared to the baseline situation.

Similarly, coronary flow (CF) can be evaluated by thermodilution technique by determining the "Mean Time Transit" (Tmn) by injecting saline at room temperature into the left coronary artery and quantifying the change in temperature of the "blood-saline mixture" between 2 temperature sensors of an intracoronary guidewire positioned distally in the artery to be evaluated. Thus, CF would be the inverse of Tmn, and CFR would correspond to the ratio between CF at maximum hyperemia and CF at rest, which accounts for the capacity of the coronary bed to increase CF in situations of high energy requirements that require an increase in cardiac output and thus the coronary flow necessary for the myocardium to cope with this increase in cardiac output. It is determined as follows (11):

| **Coronary Flow (CF)** | |
| --- | --- |
| 1  CF =  Tmn | |
| **Coronary Flow Reserve (CFR)** | |
| Coronary Flow at Hyperemia 1 / Tmn Hyp Tmn Rest  CFR = = =  Coronary Flow at Rest 1 / Tmn Rest Tmn Hyp | |
| CF | Coronary Flow |
| Tmn | Mean Time Transit |
| CFR | Coronary Flow Reserve |
| Normal value of CFR | ≥ 2.0 |

Table 2. Coronary Flow (CF) and Coronary Flow Reserve (CFR)

**-** **Index of Microvascular Resistance (IMR)**(12)**.**

The IMR is an index developed to evaluate the resistance of the microvascular compartment. Following "Poiseuille's law”, combined with the principle of maximal hyperemia generation, the pressure at the distality of the macrovascular bed and the Tmn at maximal hyperemia are determined.

Based on these assumptions, a coronary index highly related to microvascular dysfunction is obtained as follows.:

| **Coronary Flow at Hyperemia** | | |
| --- | --- | --- |
| 1  Q Hyp =  Tmn Hyp | | |
| **Index of Microvascular Resistance (IMR)** | | |
| ΔPmicrov Hyp P at Distal LAD (Pd) – P Venous Sinus (Pv)  IMR = =  Q Hyp 1 / Tmn Hyp | | Dado que  Pv ≈ 0 |
| IMR = Pd × Tmn Hyp | | |
| Q Hyp | Coronary Flow at Hyperemia | |
| Tmn Hyp | Mean Time Transit at Hyperemia | |
| ΔPmicrov Hyp | Transmicrovascular Gradient at Hyperemia | |
| Normal value of IMR | < 25 | |

Table 3. Index of microvascular resistance.

**- Fractional Flow Reserve (FFR)**(13,14)**.**

The FFR is a coronary hyperemic index that allows a functional evaluation of epicardial lesions, also based on the linear relationship between pressure and flow in the coronary tree during maximum hyperemia.

On this basis, the translesional pressure gradient generated by an epicardial stenosis is proportional to the pressure drop across the lesion. Therefore, an FFR value of 0.60 for an epicardial lesion would correspond to a 40% reduction in coronary flow at maximum hyperemia (or coronary reserve), attributable to that coronary lesion compared to the same artery if it did not present such stenosis. It is an index with a large body of evidence and is the gold standard of coronary indices for determining ischemia related to macrovascular compartment disease. It is determined as follows:

| **Fractional Flow Reserve (FFR)** | | |
| --- | --- | --- |
| At Hyperemia:  P distal to lesion (Pd) - P at Venous Sinus (Pv)  FFR =  P in the aorta (Pa) – P in the venous sinus (Pv) | | Dado que  Pv ≈ 0 |
| At Hyperemia:  Pd  FFR =  Pa | | |
| Normal value of FFR | > 0.80 | |

Table 4. Fractional Flow Reserve (FFR).

**- ‘Resting full cycle ratio’ (RFR) y `Adjusted Resting Full-Cycle Ratio´ (RFRa)**(15)**.**

Given the need to induce maximum hyperemia for the evaluation of FFR using vasodilator drugs that could cause adverse reactions and/or hinder the generalization of physiological assessment techniques for epicardial lesions, resting or nonhyperemic coronary indices were developed for the assessment of the macrovascular compartment. These are indices that do not require drug administration and have a high correlation with FFR values.

Among these indices, the RFR stands out. This is an index that, without the need for vasodilators, allows the hemodynamic significance of epicardial lesions to be assessed by identifying the lowest value of the pressure ratio distal to the stenosis (Pd) / aortic pressure (Pa) during the entire cardiac cycle at rest and, unlike other resting indices, its measurements are less dependent on the morphology of the pressure waves, the electrical signal and the phasic variations in microcirculatory resistance.

However, although the correlation between RFR and FFR is good, a non-negligible percentage of lesions can be misclassified using FFR as a reference. Therefore, in our group, we have developed the RFRa index that allows adjustment for differences based on other clinical and/or angiographic parameters, thus increasing the concordance between techniques.

| **Resting Full-Cycle Ratio (RFR)** | |
| --- | --- |
| Pd  FFR = Lowest value of during whole cardiac cycle  Pa | |
| **Adjusted Resting Full-Cycle Ratio (RFRa)** | |
| RFRa = 0.009 + 0.912*RFR + 0.023*CKD - 0.019*Non-LAD - 0.017*ACS – 0.005*IHD | |
| CKD | Chronic kidney disease |
| Non-LAD | Non-left anterior descending artery lesions |
| ACS | Acute coronary syndrome |
| IHD | Prior ischemic heart disease |
| Normal value of RFR | > 0.89 |
| Normal value of RFRa | > 0.8172 |

Table 5. Resting Full-Cycle Ratio. Adjusted Resting Full-Cycle Ratio.

**- Computational angiographic models for the evaluation of coronary compartments**(16)**.**

# Based on the principles above and computational flow dynamics, computational models have been developed that allow estimation of the involvement of the coronary compartment using angiography-based coronary indices based on angiography. Quantitative Flow Ratio (QFR) is an index that has been shown to correlate well with FFR, being superior to conventional angiography in assessing potential ischemia generated by epicardial coronary lesions. In addition, more recently, coronary indices based on angiography have even been developed that allow the estimation of microvascular resistance without the need to use pressure guides, such as the "Angiography-derived Index of Microcirculatory Resistance" (IMRangio).

**- Acetylcholine coronary vasoreactivity test** (1)**.**

Under normal conditions, an artery with a healthy endothelium responds to acetylcholine with release of nitric oxide, generating vasodilatation. In cases of blocking the action of the enzyme nitric oxide synthase or denuding the arterial wall of the endothelium, vasoconstriction is generated on the contrary, secondary to a stimulation of smooth muscle muscarinic receptors, not counteracted by nitric oxide of endothelial origin. Therefore, acetylcholine infusion can be used to assess endothelial function and adequate coronary vessel tonicity. A relevant percentage of patients with angina without associated obstructive coronary artery disease may present with this type of alteration. Although different methods have been used to reveal this entity, currently the most widely used currently is the intracoronary acetylcholine infusion test. Its objective to determine the presence of endothelial dysfunction or tonic alterations is based on the reproduction of symptoms, the triggering of vasoconstriction and the detection of electrocardiographic alterations. The evaluation of the results of this test is detailed below:

| **Intracoronary Acetylcholine Infusion Test: Diagnostic Criteria** | |
| --- | --- |
| - Negative with vasodilator response (normal):   -Non-clinical  -No ECG changes  -Vasodilation after Ach (with respect to baseline) | - Negative with vasoconstrictor response:   -Non-clinical  -No ECG changes  -No constriction ≥ 90% (with respect to NTG)  -Mild vasoconstriction (with respect to baseline) |
| - Epicardial vasospasm:   -Symptom recurrence  -ST rise or fall  -Constriction ≥ 90% (with respect to NTG) | - Microvascular vasospasm:   -Symptom recurrence  -ST-segment elevation  -No constriction ≥ 90% (with respect to NTG). |

Table 6. Intracoronary acetylcholine infusion test.

**- MicroRNAs and cardiovascular disease**

**- Synthesis and function of microRNAs.**

In the human genome, protein-coding genes represent only 1.1%, whereas more than 70% of the genome is transcribed giving rise to noncoding RNA (nc-RNA) that play important roles in the regulation of pathophysiological processes and cellular homeostasis.

miRNAs are a type of small nc-RNA (17 to 25 nucleotides) that play an important role in the regulation of gene expression. To date, miRNAs are the most studied and described nc-RNAs in the literature (17).

The initial concept that miRNAs regulate gene expression was developed almost 30 years ago, in 1993 in the laboratories of Ambros and Ruvkun when studying the development of the nematode *Caenorhabditis elegans* (18). Several studies have shown that miRNAs are evolutionarily conserved across species and are often ubiquitously expressed (19) (20)(21)

miRNAs can negatively regulate gene expression at the post-transcriptional level by binding to messenger RNA (mRNA) and causing gene silencing by inhibiting translation and/or degradation of mRNA; as well as activating the transcription of certain target genes. MiRNAs have been estimated to control the activity of 30-50% of protein-coding genes, playing an important role in the regulation of several biological processes, including embryogenesis, cell proliferation and differentiation, apoptosis, or tumorogenesis (22).

In the cardiovascular system, miRNAs regulate various processes including cardiomyocyte growth and contractility, heart rhythm development and maintenance, plaque formation, lipid metabolism, and angiogénesis (6). Altered expression of certain miRNAs can be found in blood samples from patients with various cardiovascular diseases, making them attractive candidates as biomarkers.

**- Potential of microRNAs as biomarkers.**

Although miRNAs were initially described as intracellular regulators, they have been stably detected in body fluids. Extracellular microRNAs participate in intercellular communication at the autocrine, paracrine, and endocrine levels and have been implicated in both physiological and adaptive responses, as well as in the emergence and development of disease states. Thus, the concentration and extracellular composition of miRNA reflect pathophysiological states and provide information on the molecular phenotype of the patient under different conditions (23–26).

As reviewed by our group, extracellular miRNAs have the optimal biochemical properties to become excellent biomarkers: (a) they can be obtained by minimally invasive techniques in clinical samples; b) they are highly stable and have a long half-life within the sample; c) they can be quantified by standard techniques already available in clinical laboratories: quantitative reverse transcription PCR (qPCR); d) global profiles could be obtained in a single experiment by RTqPCR, or relatively accessible techniques such as next-generation sequencing or microarrays (27). Based on these characteristics, the circulating miRNA profile constitutes a new generation of biomarkers in various cardiovascular diseases.

**- Relationship between microRNAs and cardiovascular disease: summary of the evidence.**

Currently, many miRNAs are already associated, through different pathophysiological mechanisms, with cardiovascular disease. In the following, we summarize the current evidence on the main miRNAs evaluated in clinical scenarios related to the object of our research, namely atherosclerosis and coronary artery disease.

| **miRNAs and atherosclerosis** | |
| --- | --- |
| miR-126-3p | One of the first miRNAs identified in the development of atherosclerosis.  It is highly expressed in endothelial cells and its expression is essential in vascular development.  Reduced levels favor plaque formation.  Inhibits the expression of VCAM-1, a molecule expressed by endothelial cells that allows the adhesion and migration of leukocytes to the vascular wall(28) |
| miR-21-5p | Related to the early stages of the atherosclerotic process in patients with arterial hypertension (29). |
| miR-155-5p | Expression induced by TNF-α and IFN-β. Increases the population of granulocytes and monocytes during inflammation. Also regulates the expression of the AT1R gene (angiotensin II type 1 receptor) found to be associated with the regulation of blood pressure and atherosclerosis (30). |
| miR-143-5p, miR-145-5p | They are expressed in vascular smooth muscle cells (VSMC) and inhibit migration and proliferation within the developing atherosclerotic plaque (31) |
| miR-133a-5p | Inhibits the growth and proliferation of vascular smooth muscle cells (32) |
| miR-122 -5p | It favors atherosclerosis through the regulation of cholesterol homeostasis. It also promotes inflammation and myocardial fibrosis (33) |
| miR-100-5p | It suppresses the expression of endothelial adhesion molecules attenuating the interaction between the endothelium and leukocytes and reducing inflammation of atheromatous plaques (34) |
| **miRNAs and coronary artery disease** | |
| miR-1-3p, miR-133a-3p, miR-208a-3p, miR-499a-5p | They are overexpressed in patients with acute coronary syndrome and are related to the extent of damage and the prognosis of the patient (35,36). |
| miR-126-3p, miR-17-5p, miR-92a-3p | Infra expression of these miRNAs in patients with stable coronary artery disease compared to healthy subjects (37). |
| miR-126-3p | It has shown a positive association with AMI in the general population in a 10-year follow-up (prospective study) (38) |
| miR-197-3p, miR-223-3p | It has been shown to have a positive association with AMI in the general population (39) |
| miR-126-3p, miR-145-5p | The presence of transcoronary gradients is related to the presence of unstable atheromatous plaques. (40) |
| miR-1-3p | Inhibits Spred1 gene expression and promotes angiogenesis and collateral circulation formation. In relation to cardiogenesis and regulation of stem cell differentiation in cardiomyocytes. (41,42) |
| miR-214-3p | Its levels correlate with the expression of vascular endothelial growth factor. An increase in the concentration of this RNA can be used to predict the presence and severity of coronary lesions in patients with coronary artery disease (43) |
| miR-499a-5p | Highly enriched in the embryonic heart  - Involved in late cardiogenic stages  - Responsible for terminal differentiation of myoblasts to cardiomyocytes and fast/slow muscle fiber specification (44,45) |
| miR-208a-3p | Involved in the late stages of cardiac development.  - Related to the cardiomyocyte involvement of myoblast cardiomyocytes.  - Regulates the expression of cardiac myosin heavy chain (the major contractile protein) (44) |
| miR-142 | Potential marker for predicting MACE in patients with coronary artery disease after percutaneous coronary interventionism.(46) |

Table 7. Main microRNAs associated with cardiovascular disease (CVD) and their mode of action.

**- Variability of microRNAs in published studies.**

As mentioned above, the evidence on miRNAs has increased significantly in recent years. However, it is important to note that the usefulness of miRNAs as biomarkers can vary between studies. Factors such as the clinical setting, the type of sample, as well as the time of collection and its processing, can affect the results reported in different studies (42-48). A recent meta-analysis analyzing and comparing miRNAs isolated in patients with coronary artery disease with respect to healthy subjects showed overexpression of certain miRNAs in patients with coronary artery disease, while other miRNAs showed inconsistent results with overexpression in some studies and underexpression in others (47). This study also shows interesting comparisons between miRNAs isolated in stable coronary artery disease and in acute coronary syndrome compared to healthy controls as shown in the following table.

| Coronary artery disease (any type) versus healthy controls |
| --- |
| Overexpression in coronary artery disease: miR-1-3p, miR-499a-5p, miR-133a-3p, miR-208a-3p/208b-3p, miR-21-5p, miR-142-5p, miR-145-5p |
| Over and under-expressed: miR-126-3p, miR-208b-5p, miR-92a-3p, miR-145-5p y miR-142-5p |
| Stable coronary artery disease versus healthy controls. |
| MiR overexpressed: miR-125a-5p, miR-187-3p, miR 502-5p |
| Underexpressed MiRs: miR-145-5p, miR-29b-3p, let-7 |
| Over- and under-expressed: miR-126-3p, miR-155-5p, miR-17-5p, miR-92a-3p |
| Acute coronary syndrome versus healthy controls. |
| MiR overexpressed: miR-1-3p, miR-499a-5p, miR-208a-3p/208b-3p, miR-133a-3p, miR-133b-3p, miR-27a-3p, miR-30e-5p, miR-93-5p, miR-21-5p |
| Over- and under-expressed: let-7, miR-208b-3p, miR-126-3p, miR-145-5p, miR-134, miR-223-3p, miR-142-5p |
| Acute coronary syndrome versus stable coronary artery disease. |
| Overexpressed in acute coronary syndromes: miR-21, miR-208a-3p/208b-3p, miR-133a-3p, miR-133b-3p, miR-140-5p, miR-146a-5p, miR-499a-5p, miR-27a-3p, miR-27b-3p, miR-451a, miR-29a-3p, miR-29c-3p |
| Over and under-expressed: miR-30a-5p, let-7, miR-142-5p, miR26a-5p, miR26b-5p, miR-92a-3p, miR-150-5p, miR-22-3p, miR-223-3p |

Table 8. MicroRNAs identified in patients with coronary artery disease (stable and/or acute coronary syndrome). In green microRNAs with underexpression. In red microRNAs with overexpression. In yellow microRNAs with over/under expression. (47)

Therefore, despite the large volume of literature on miRNAs in different heart diseases, we must be cautious when interpreting the data offered by the different studies and use a robust methodology that allows a rigorous evaluation of miRNAs in any research project that contemplates the evaluation of these biomarkers.

**HYPOTHESIS**

Different patterns of coronary artery involvement are associated with the overexpression or underexpression of specific miRNAs.

**PRIMARY OBJECTIVE**

Characterization of miRNA expression as a function of the coronary compartment in patients with chest pain.

**SECONDARY OBJECTIVES**

1.- To evaluate the association of miRNA expression with the degree of involvement of the stenosis and the extent of epicardial coronary artery.

2.- To evaluate the association of miRNAs levels with angiography-based indices for determination of coronary compartments.

3.- To evaluate the association of miRNA expression with the presence of cardiovascular risk factors and/or established vascular disease.

4.- To evaluate the association of miRNA expression with other hematological and biochemical markers.

**MATERIAL Y METHODS.**

**- Recruitment.**

Patients with angina referred for coronary angiography at the Universitary Hospital Arnau de Vilanova University Hospital in Lleida will be included. After confirming that the patients are eligible for the study and have signed the informed consent form (**Appendix 1**), the patients will be included in the study.

**- Inclusion criteria:**

1. Age ≥ 18 years.
2. Patients with chest pain suggestive of angina evaluated by a cardiologist referred for diagnostic coronary angiography and eventual coronary angioplasty.
3. Echocardiogram ruling out non-coronary cardiac causes of chest pain.
4. Informed consent.

**- Exclusion criteria:**

1. Contrary to allergy not susceptible to receive pre-medication.
2. Severe bronchial asthma or intolerance to adenosine.
3. Atrioventricular block (≥ 2nd degree) or intolerance to acetylcholine.
4. Acute myocardial infarction with elevation of the ST segment.
5. Acute myocardial infarction without elevation of the ST segment.
6. Cardiogenic shock.
7. Total occlusion of any coronary artery that prevents measurement with pressure-temperature guides.
8. Previous coronary bypass.
9. Women who may be pregnant.
10. Renal dysfunction with estimated glomerular filtration rate < 30 mL/min/1.73m2.
11. Inability to understand the nature of the study and/or sign the informed consent.
12. Any other medical condition that, in the opinion of the investigator, may cause safety problems for the patients or may alter the results of the study.

* NOTE: Given that, in routine clinical practice, a significant proportion of patients are referred for coronary angiography without a previous positive ischemia detection test and even with a negative ischemia detection test in the presence of a high suspicion of anginal pain, in our study the presence of an ischemia detection test is not mandatory for inclusion in the study and it is at the discretion of the referring cardiologist to request coronary angiography.

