**- Selection of microRNAs and other samples.**

It is essential to determine those miRNAs that have shown only over- or under-expression in previous studies of coronary atherosclerosis or stable coronary artery disease, i.e:

- Overexpression: miR-1-3p, miR-21-5p, miR-133a-3p, miR-133b-3p, miR-208a-3p,

miR-208b-3p, miR-125a-5p, miR-187-3p, miR-499a-5p, miR-502-5p.

- Under expression: miR-100-5p, miR-143-3p, miR-145-3p, miR-29b-5p.

Furthermore, since miRNA determination kits allow the analysis of multiple miRNAs in each sample, other potential candidates will be determined in agreement with the molecular biology experts. Samples corresponding to routine practice, such as blood counts, biochemistry, lipids, etc., will also be collected.

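### Eligibility names only acute STEMI and NSTEMI, with no look-back, so unstable angina and recent infarction are kept out only at the investigator's discretion, while half of the named miRNA panel is listed as raised in acute coronary syndrome

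*Protocol*

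**What the plan says.** Protocol, Exclusion criteria, items 4 and 5, remove "Acute myocardial infarction with elevation of the ST segment" and "Acute myocardial infarction without elevation of the ST segment". Item 6 adds cardiogenic shock. None of these carries a time window, and neither unstable angina nor recent infarction is named anywhere in the list. Item 12 leaves to the investigator any other medical condition that "may cause safety problems for the patients or may alter the results of the study".

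Protocol, Inclusion criteria, item 2, admits "Patients with chest pain suggestive of angina evaluated by a cardiologist referred for diagnostic coronary angiography and eventual coronary angioplasty". It does not require the presentation to be stable or chronic.

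Protocol, Selection of microRNAs and other samples, says that the panel consists of "those miRNAs that have shown only over- or under-expression in previous studies of coronary atherosclerosis or stable coronary artery disease". It names 14: ten over-expression and four under-expression candidates. Further candidates may be added.

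Protocol, Variability of microRNAs in published studies, Table 8, has separate rows for ACS versus healthy controls, stable disease versus healthy controls, and ACS versus stable disease. The last of these begins "Overexpressed in acute coronary syndromes: miR-21, miR-208a-3p/208b-3p, miR-133a-3p, miR-133b-3p".

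Groups 1 to 4 are defined from FFR, IMR and CFR. Group 4 (non-coronary pain) is the control, and the target is 25 patients per group.

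**The concern.** The primary objective is miRNA expression by coronary compartment. For a difference between groups to be read that way, the groups should not also differ in how acute the patients were when blood was drawn. The eligibility text does not secure this, and the protocol's own literature table lists many of the chosen markers as responding to acuity.

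Groups 1 and 2 are defined by FFR ≤ 0.80. It is plausible, though the protocol gives no figures, that patients with unstable or post-infarction pain fall there more often than in Group 4. A marker that rises with the acute event would then separate macrovascular from non-macrovascular groups without any compartment effect. Blood is taken once, before angiography, so a stable-phase sample cannot be obtained afterwards. The Statistical analysis section names Mann-Whitney comparisons and says nothing about presentation. An analysis plan that is not shown might address that, but it would not change who is admitted.

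**Working it through.** **1. Who is removed by a fixed rule?**

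| Presentation | Named exclusion | Other barrier |
|---|---|---|
| Acute STEMI | item 4 | – |
| Acute NSTEMI | item 5 | – |
| Unstable angina | none | item 12, discretionary |
| Infarction days or weeks earlier, no longer acute | none (no look-back) | item 12, discretionary |

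**2. How much of the panel is listed as raised in ACS?** The 14 names were matched with Table 8 by exact name. The one exception is miR-21 in the row for ACS versus stable disease, which is read as miR-21-5p.

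| Table 8 row | Panel members | Of 14 | Of the 10 over-expression candidates |
|---|---|---|---|
| Raised, ACS vs healthy | 1-3p, 21-5p, 133a-3p, 133b-3p, 208a-3p, 208b-3p, 499a-5p | 7/14 = 50% | 7/10 = 70% |
| Raised, ACS vs stable | the same without 1-3p | 6/14 = 43% | 6/10 = 60% |
| Raised, stable vs healthy | 125a-5p, 187-3p, 502-5p | 3/14 = 21% | 3/10 = 30% |

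Table 8 also lists miR-208b-3p as inconsistent in ACS versus healthy controls. Without it the first count is 6/14. None of the four under-expression candidates appears in Table 8 under its exact name.

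The comparison closest to mixing acute and stable patients is ACS versus stable disease, so 6 of 14 is the most relevant count.

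**3. What could this do to a group comparison?** The protocol states no figure to reproduce.

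- Inputs from the protocol: 25 patients per group, Mann-Whitney test, alpha 0.05.
- Assumed: two-sided testing; the share of acute patients in each group; the shift of a marker in acute patients, in SD units; otherwise normal data with unit SD and no true compartment effect.
- Spurious mean difference = (share in the FFR ≤ 0.80 group − share in the comparison group) × shift.
- Rejection rate by simulation, 8,000 pairs of groups per setting.

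| Acute shares | Shift | Spurious difference | Rejection rate per miRNA |
|---|---|---|---|
| 20% vs 5% | 1 SD | 0.15 × 1 = 0.15 SD | 0.070 |
| 20% vs 5% | 2 SD | 0.15 × 2 = 0.30 SD | 0.114 |
| 30% vs 5% | 1 SD | 0.25 × 1 = 0.25 SD | 0.112 |
| 30% vs 5% | 2 SD | 0.25 × 2 = 0.50 SD | 0.234 |
| 40% vs 10% | 1 SD | 0.30 × 1 = 0.30 SD | 0.155 |
| 40% vs 10% | 2 SD | 0.30 × 2 = 0.60 SD | 0.332 |

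With no shift the rate is about 0.05. Repeat simulations agreed to within about 0.01.

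**4. Which contrasts are exposed?** On this reasoning, they are Groups 1 or 2 against Groups 3 or 4. Group 1 versus 2 and Group 3 versus 4 would be little affected, because acuity would be similar on both sides.

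**The case against.** The strongest case on the other side is that this is a request for clarification and not a demonstrated bias. Several stronger readings are tempting, and the documents do not support them.

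- **That most of the panel rises in ACS.** It is half of the 14 named miRNAs. The figure of 7 in 10 holds only for the over-expression list.
- **That Table 8 proves an effect in the patients who could slip through.** Table 8 does not divide ACS into infarction and unstable angina. Table 7 links four of the seven (miR-1-3p, 133a-3p, 208a-3p, 499a-5p) to the extent of damage, and acute infarction is already excluded. Nothing in the protocol shows these markers to be raised in unstable angina or weeks after an infarction. This stands, and it is the main limit on the point.
- **That the protocol expects acute patients,** because the RFRa formula contains "0.019*Non-LAD - 0.017*ACS". The group had already developed that index. A prediction formula keeps its covariates in a narrower population, so the term says nothing about intended enrolment.
- **That the panel was chosen for stable disease alone.** The stated source is coronary atherosclerosis or stable disease.
- **That such patients will be enrolled.** Item 12 extends beyond items 1 to 11 and can reach them, and a single centre limits uneven use. It remains a judgement made patient by patient, however, and not a fixed rule.

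It is also fair that breadth may be intended. The objective speaks of patients with chest pain, and a secondary objective covers established vascular disease. If so, the protocol should say that recent and unstable presentations are accepted.

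**Conclusion.** The gap in the eligibility text is real. Unstable angina and infarction that is no longer acute are excluded by no named criterion, in a study whose panel rationale is atherosclerosis or stable disease and whose own table lists 7 of 14 candidates as raised in ACS versus healthy controls and 6 of 14 versus stable disease.

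The consequence is possible but not shown. It needs three things that the protocol does not give: an appreciable share of such patients, their concentration in the FFR ≤ 0.80 groups, and a marker shift that persists outside acute infarction. If all three hold, the assumed settings give a false-positive rate per miRNA of about 7% to 33%. At the low end this is barely above the nominal 5%. These figures illustrate sensitivity and do not estimate the trial's error rate.

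The point should be fixed, with moderate confidence, because it touches the primary comparison and costs little to settle.

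**What to change.** Reconcile the inclusion and exclusion criteria with the panel rationale. State explicitly whether unstable angina and recent infarction are eligible and, if a look-back before the blood sample is wanted, state its length. Both are clinical decisions for the sponsor; the protocol offers no basis for a particular window.

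Whatever is decided, repeat the primary comparison without ACS patients. The ACS status is already needed to compute RFRa, so no new procedure is required. Table 5 does not say what period its ACS term covers, so the date of any earlier infarction should be recorded too. Report the number of ACS patients in each group, so that a reader can see whether acuity is in fact uneven.

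Cost: an amendment of a few lines, possibly slower recruitment, and slightly fewer patients in the sensitivity analysis. The unit reports more than 1,110 diagnostic angiograms a year for a target of 100 patients, although the protocol does not say how many of them would qualify.
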